Thus, it is pertinent to look for effective psychotherapeutic interventions for people with PTSD that can be implemented online, facilitating the immediate availability of mental health care, regardless of the geographic region. Because of the empirical support that cognitive behavioral therapy (CBT) [12,13,14,15] and prolonged exposure therapy (PE) [16,17,18] have received, they are currently the first-line treatments for PTSD [19].

Available PTSD treatments have been shown to have a high non-response and dropout rate. A review of the literature of 55 studies of PTSD patients found non-response rates as high as 50% and dropout rates ranging widely and depending on the nature of the study population [20]. In a meta-analysis assessing war trauma [21], dropout rates ranged from 5% to 78%, and in a recent review of data from three clinical trials of evidence-based PTSD treatments in military service members, the dropout rate was 31% [22]. These findings suggest new and innovative strategies are needed to improve treatment retention, especially in a new and complex situation such as the COVID-19 pandemic. Thus, testing treatments for PTSD with lower potential for dropouts might still be necessary [23,24]. Recently, Duran et al. [25] showed that TBCT had a low dropout rate in PTSD relative to PE.

TBCT [26,27,28] is a novel and innovative transdiagnostic approach [29] shown to be effective for depression [30], social anxiety disorder [31,32,33,34], PTSD [25] and obsessive-compulsive disorder (Rodrigues et al., accepted). TBCT differs from other CBT approaches in that it introduces a new, organized and systematic approach to change dysfunctional negative core beliefs (CBs), while allowing cognitive, emotional and experiential work to be done conjointly [28]. While incorporating a courtroom metaphor to challenge dysfunctional CBs conceptualized as self-accusations, TBCT is an example of assimilative psychotherapy integration that relies on Beckian CBT, incorporating and integrating components of other psychotherapies [28,35].

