### 2.10. Sample Size

The sample size calculation was estimated using the G*Power software version 3.1 [76], considering a mixed design. Parameters that were taken into account were the F test and repeated measures ANOVA for comparison between groups, for an effect size of 0.25, α criterion of 0.05 and power of (1−β) 0.80, three groups design (TBCT X MBHP X WBT), three measures (baseline, mid-treatment and final assessment), and an a priori correlation between the repeated measures of 0.50. Hence, a sample of 108 participants was obtained, with a numerator of 2 and a denominator of 105 degrees of freedom, for a critical F of 3.08. Considering a 25% dropout rate, a total of 135 participants was estimated.

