### 2.15. Statistical Methods

The collected data will be analyzed statistically using the Statistics Package for Social Science software (SPSS), version 24.0 [77]. Clinical and demographic categorical variables will be analyzed with *X*^2^ (sex, education, color or race, and dropout rate) and continuous variables will be assessed with one-way ANOVA (age and scale scores). Missing data for both primary and secondary outcome measures will be analyzed by intention to treat (ITT) and multiple imputation (IM), with five imputed databases taking baseline and sociodemographic data and assuming the random chance mechanism. Generalized estimation equations (GHG), taking time as a covariate, will be performed to compare changes in scores over time and between groups (TCP, MBSR and PP). Effect sizes will be evaluated according to Cohen’s tests. The assumed level of statistical significance will be 0.05.

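### Section 2.15 fixes the number of imputed data sets at five, which leaves avoidable seed-to-seed variation in the CAPS-5 p-value when the result is near 0.05

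*Protocol article*

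**What the plan says.** Section 2.15 (Statistical Methods) applies intention to treat and multiple imputation to missing primary and secondary outcome data, "with five imputed databases taking baseline and sociodemographic data and assuming the random chance mechanism". GEE is then used to compare change over time between the three groups, and "The assumed level of statistical significance will be 0.05".

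Section 2.10 (Sample Size) sets the likely scale of missing data: "Considering a 25% dropout rate, a total of 135 participants was estimated". The primary outcome is CAPS-5 (section 2.8), and allocation is 1:1:1 (section 2.13), so 45 patients per arm.

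The number five is written into the plan. It is a stated choice, not a detail left for an analysis plan that is not shown.

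**The concern.** With five imputations, the between-imputation variance is estimated on 5 − 1 = 4 degrees of freedom, and the pooled estimate averages only five random draws. Two analysts with the same data and the same imputation model but different seeds can therefore get visibly different standard errors and p-values. The usual defence of five is relative efficiency, which is still about 95% here. That figure describes average precision. It does not say how far the p-value moves when the same data are imputed again.

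What is at stake is whether a CAPS-5 comparison close to 0.05 is declared significant because of the data or because of the seed. Such a result is not far-fetched in a trial of three active therapies powered at 0.80.

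**Working it through.** **1. The plan's own sample size.** The inputs in section 2.10 are "for an effect size of 0.25, α criterion of 0.05 and power of (1−β) 0.80, three groups design" and "three measures (baseline, mid-treatment and final assessment), and an a priori correlation between the repeated measures of 0.50". For the between-groups test of a repeated-measures ANOVA, the noncentrality is λ = f² · N · k / (1 + (k − 1)ρ). With f = 0.25, k = 3, ρ = 0.5 and N = 108, λ = 0.0625 × 108 × 3 / 2 = 10.125. Power is 0.809, with 2 and 105 degrees of freedom and critical F 3.083. N = 105 gives 0.797, so the stated 108 is reproduced.

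**2. Range for missing data.** The stated 135 is 108 × 1.25, and 1 − 108/135 = 0.20. The allowance is therefore 25% by its label and 20% by its arithmetic. Both are used below as assumed fractions of missing final CAPS-5 scores.

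**3. Approximate size of the seed effect.** Across seeds, the pooled estimate varies with variance B/m, where B is the between-imputation variance and m the number of imputations. Dividing by the total variance, the pooled z has a seed-to-seed SD of about √(FMI/m), where FMI is the fraction of missing information. FMI is an assumption. It should be close to the missing fraction, because section 2.15 names only baseline and sociodemographic predictors.

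| FMI | m | SD of z | p of 0.05 moved by ±1 SD | Relative efficiency 1/(1 + FMI/m) |
|---|---|---|---|---|
| 0.15 | 5 | 0.17 | 0.033 to 0.074 | 0.971 |
| 0.20 | 5 | 0.20 | 0.031 to 0.078 | 0.962 |
| 0.25 | 5 | 0.22 | 0.029 to 0.083 | 0.952 |
| 0.25 | 50 | 0.07 | 0.042 to 0.059 | 0.995 |
| 0.25 | 100 | 0.05 | 0.044 to 0.056 | 0.998 |

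This leaves out the noise in the pooled standard error itself, so it understates the spread at m = 5.

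**4. Simulation at a fixed large-m p-value.** Set-up: 3 × 45 patients; baseline-to-final correlation 0.5; 20% or 25% of final scores missing completely at random; imputation from baseline, arm and two demographic variables; an ANCOVA contrast of two arms; Rubin pooling with Barnard-Rubin degrees of freedom. The data were set so that the p-value with very many imputations took a chosen value, and imputations were then redrawn. The mean simulated FMI was 0.203 and 0.253, as assumed in step 3.

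With a large-m p of 0.05 and 25% missing, the central 95% of p-values over seeds was 0.014 to 0.18 at m = 5, 0.027 to 0.094 at m = 20, 0.034 to 0.074 at m = 50 and 0.038 to 0.066 at m = 100. With 20% missing, m = 5 gave 0.017 to 0.16.

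Share of seeds that put the result on the wrong side of 0.05:

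| Missing | Large-m p | m = 5 | m = 20 | m = 50 | m = 100 |
|---|---|---|---|---|---|
| 20% | 0.03 | 29% | 6% | 0.4% | 0% |
| 25% | 0.03 | 32% | 8% | 1% | 0.1% |
| 20% | 0.08 | 15% | 3% | 0.3% | 0% |
| 25% | 0.08 | 19% | 5% | 0.6% | 0% |

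**5. A borderline band instead of one value.** In a separate simulation with the same arm size, correlation and type of contrast, data sets were kept if their 200-imputation p lay between 0.02 and 0.04. Seeds giving p above 0.05 were 27% (20% missing) to 32% (25% missing) at m = 5, about 2% to 6% at m = 50, and about 0% to 4% at m = 100.

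**6. Without selecting borderline data.** At an assumed standardised difference of 0.5, m = 5 and m = 200 disagreed about 0.05 in roughly 10% of data sets (9% to 12% over two sets of runs). With no true effect they disagreed in about 2% to 3%. Type I error was 4.5% to 5.9% at m = 5 and 4.5% to 5.8% at m = 200. Power at m = 5 was 3 to 5 points lower.

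**The case against.** **The large percentages are conditional.** The 27% to 32% applies only to results already near the threshold. This stands, and the unconditional figure of roughly 10% should be read beside it. A clear result in either direction is little affected.

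**The inference remains valid.** This also stands. Rubin's rules allow for the small number of imputations through a wider interval, and the type I error rate is unchanged. A reader might infer that five imputations bias the CAPS-5 comparison or inflate false positives. Neither the plan nor the calculation supports that.

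**Missingness may be lower.** The 25% is a dropout allowance, not a stated rate of missing outcomes, and under intention to treat a patient who stops therapy may still be assessed. This stands as a limit on the inputs. A reader might instead take the 31% dropout quoted in the Introduction as a harsher planning case. It comes from trials in military service members, is cited to motivate therapies with better retention, and is not a planning figure for this trial.

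**The planned analysis is GEE, not ANCOVA.** This is a fair limit on the exact percentages. A change-score contrast with robust variance, standing in for the GEE time-by-arm term, gave similar results for large-m p between 0.02 and 0.04. At 25% missing, 29% of seeds crossed at m = 5 and 3% at m = 50; at 20% missing, 24% and 2%. Adding a fully observed mid-treatment score to the imputation model left 27% and 23% at m = 5.

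**Any finite number of imputations depends on the seed.** True, and there is no sharp cut-off: 20 imputations already remove much of the problem. Very close to 0.05 some dependence remains at 50 or 100. A fixed seed alone makes the run repeatable, but an arbitrary draw still decides the result.

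**Conclusion.** The point holds as one of reproducibility. Fixing five imputations leaves avoidable Monte Carlo noise in the primary p-value and interval, and costs a little power. For a result whose stable p-value is 0.02 to 0.04, roughly three seeds in ten would reverse the significance statement. Over all data sets at a standardised difference of 0.5, about one in ten would be read differently than with 200 imputations.

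These sizes rest on assumptions the plan does not state: 20% to 25% of final CAPS-5 scores missing completely at random, a baseline correlation of 0.5, and a single ANCOVA contrast in place of the GEE. The direction is secure and the exact percentages are not. The change is worth making because it is free, not because the planned analysis would be invalid.

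**What to change.** In section 2.15, replace the five imputed data sets with at least 50, for example 100. This is the whole of the necessary change. A pre-set seed and a reported Monte Carlo error for the primary estimate and p-value are useful additions, but they can sit in the analysis plan, and their absence from the article is no fault. The cost is one number in the text and a few minutes of computing. No extra patients, data or visits are needed.

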## Abstract

Background: Research suggests the use of different forms of therapy as a way of decreasing dropout rates in the treatment of post-traumatic stress disorder (PTSD). The psychotherapies to be assessed in this study are trial-based cognitive therapy (TBCT), mindfulness-based health promotion (MBHP) and positive psychotherapy (PPT). Objectives: (1) to assess the online efficacy of TBCT compared to MBHP and PPT to reduce the symptoms of PTSD in the context of the Coronavirus Disease 2019 (COVID-19) pandemic; (2) to compare the efficacy of these psychotherapies in improving anxiety, depression, guilt and in promoting well-being; and (3) to describe how professionals perceive online treatment. Methods: A randomized, multicenter, single-blind clinical trial will be conducted, with three separate arms. An estimated sample of 135 patients will receive either TBCT, MBHP or PPT and will be treated through online, individual, weekly visits, totaling 14 sessions. The primary outcome will be CAPS-5 and secondary outcomes will be HADS and WHO-5. The variables used to mediate these outcomes will be the Trauma-Related Guilt Inventory (TRGI), Negative Core Beliefs Inventory (NCBI) and the California Psychotherapy Alliance Scale (CALPAS-P). Expected results: PTSD symptoms are expected to be reduced after TBCT, MBHP and PPT. No statistical difference is expected to be found among the three. Discussion: The present study will evaluate and contribute towards the development of new psychotherapeutic options for patients with PTSD. The results of this study will allow the dissemination of new effective and adaptable interventions for patients with PTSD.

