It has also been demonstrated in a randomized clinical trial (*N* = 36) comparing TBCT techniques to conventional CBT techniques that TBCT was as efficacious as conventional CBT techniques in reducing social anxiety symptoms and improving quality of life and more efficacious than CBT in reducing fear of negative evaluation, social avoidance and distress [31,34]. A second study aiming to evaluate the efficacy of TBCT for generalized social anxiety disorder in a population with high rates of comorbid disorders, especially depression [33], was carried out. This was a two-arm randomized clinical trial that included 39 adults (TBCT = 18; waitlist group = 21), and symptom severity was assessed at pre- and post-treatment. Reductions in social anxiety, social avoidance and depression were observed in the participants in the TBCT group, of which all were associated with a large effect size, while no differences between pre- and post-treatment scores were observed in the waitlist condition. Interestingly, patients with comorbid conditions showed greater reductions in social anxiety symptoms across treatment relative to those with SAD only.

A study (*N* = 76) comparing the efficacy of TBCT, behavioral activation (BA) and treatment as usual (TAU) in the treatment of major depressive disorder [30] showed that both TBCT and BA (which also included antidepressants) were different from TAU (which included antidepressants alone) in reducing the HAM-D and BDI scores.

Recently, 95 patients who met DSM-4-TR criteria for PTSD were randomly assigned to receive either TBCT or prolonged exposure (PE) [25]. A significant reduction in the primary outcome as assessed by the Davidson Trauma Scale (DTS) was improvement in PTSD symptoms. Reductions in DTS scores were observed in both arms, but there was no significant difference between treatments. Regarding the secondary outcomes (depression, anxiety and dysfunctional attitudes assessed by the Beck Depression/Anxiety Inventories and Dysfunctional Attitudes Scale, as well as the dropout rate), significant differences in depressive symptoms were observed in favor of TBCT. In addition, the dropout rate was lower in the TBCT group than in the PE group, suggesting that TBCT may be an effective alternative for treating PTSD.

Mindfulness-based health promotion

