### 2.8. Outcomes

Primary outcomes will be assessed by the reduction in PTSD symptoms, measured through CAPS-5. Secondary outcomes will be the improvement in symptoms of anxiety, depression and well-being. Mediator variables will also be assessed, measuring negative CBs, guilt and the strength of the therapeutic alliance. All scales will be applied by a blind assessor to the intervention groups before randomization (Initial Assessment), after seven sessions (Intermediate Assessment) and after 14 sessions (Final Assessment). They will also be applied in the 3-, 6- and 12-month follow-ups. Table 1 shows the flow of sessions and evaluations over the study period. Table 1 shows the SPIRIT diagram.

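### The stated imputation rule in section 2.15 names a chance mechanism and lists no treatment arm or session-7 CAPS-5, so followed as written it pulls between-arm differences towards zero

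*Protocol article*

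**What the plan says.** Section 2.15 (Statistical Methods) gives one rule for missing primary and secondary outcomes: analysis by intention to treat with multiple imputation, using five data sets built from baseline and sociodemographic variables, "assuming the random chance mechanism". Section 2.8 makes CAPS-5 the primary outcome, so the rule governs the main comparison. CAPS-5 is also measured at session 7 (section 2.9), but that score is not among the listed inputs, and neither is treatment arm.

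On dropout, the Abstract opens with the "use of different forms of therapy as a way of decreasing dropout rates in the treatment of post-traumatic stress disorder", and the Introduction adds that "testing treatments for PTSD with lower potential for dropouts might still be necessary". Section 2.10 allows for one overall rate: "Considering a 25% dropout rate, a total of 135 participants was estimated". Section 2.15 also compares the dropout rate between groups by chi-square, apart from the efficacy analysis.

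**The concern.** There are two separate problems in one sentence.

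The first is the mechanism. If scores are lost purely by chance, loss cannot depend on which therapy a patient received. The article's rationale is that it can.

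The second is the list of inputs, and it has the more definite effect. Without arm in the model, a missing score is drawn from one regression fitted to all three groups together, so the imputed patients show no treatment difference whatever the truth. Without the session-7 CAPS-5, a patient who had responded by mid-treatment and one who had not get the same prediction if their baseline data match.

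At stake is the primary comparison. Hypothesis H1 in section 2.2 looks for a difference between TBCT or MBHP and PPT, while the Abstract expects none among the three. A rule that shrinks differences works against the first and favours the second for reasons unrelated to the therapies.

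**Working it through.** **1. The plan's own figure.** Inputs from section 2.10: f = 0.25, three groups, three measures, correlation 0.50, alpha 0.05, power 0.80. For the between-groups test, lambda = N × f² × m / (1 + (m − 1) × rho). With N = 108 this is 108 × 0.0625 × 3 / 2 = 10.125, on 2 and 105 degrees of freedom. Critical F is 3.08 and power 0.809 (N = 105 gives 0.797), so 108 reproduces. The total of 135 is 108 × 1.25, or 45 per arm under the 1:1:1 allocation. At 25% loss, 135 × 0.75 = 101 remain. How the inflation was done is a separate matter.

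**2. Leaving arm out of the imputation model.** Let each arm lose a fraction p. The imputed values have the same expected mean in every arm, given balanced baselines. The expected difference is therefore (1 − p) × true difference + p × 0.
- At p = 0.25, a true 0.5 SD becomes 0.75 × 0.5 = 0.375 SD.
- If 108 of 135 were retained, p = 27/135 = 0.20 and the result is 0.80 × 0.5 = 0.40 SD.
- As a yardstick, f = 0.25 with TBCT and MBHP equal and PPT apart means 0.25 × 3 / √2 = 0.53 SD. At p = 0.25 this becomes 0.75 × 0.53 = 0.40 SD.

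This needs no informative dropout and no imbalance in dropout.

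**3. Simulation check.** Two arms of 45, pre-post correlation 0.5, five imputations, 2,000 runs, baseline-adjusted linear model as a stand-in for the planned estimating equations, dropouts no different from prediction:

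| Dropout | Arm in model | Mean estimate, true 0.5 SD | Power | False-positive rate, true 0 |
|---|---|---|---|---|
| 25% / 25% | yes | 0.496 | 58% | 4.8% |
| 25% / 25% | no | 0.378 | 37% | 1.2% |
| 15% / 35% | yes | 0.501 | 57% | 5.0% |
| 15% / 35% | no | 0.362 | 32% | 0.8% |

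With arm in the model, unequal dropout alone causes no bias. With arm left out, the estimate shrinks by about a quarter and the test becomes conservative.

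**4. Leaving out session 7.** With equal correlations of 0.50, baseline alone explains 0.5² = 0.25 of the variance in the final score. Baseline and session 7 together explain 2 × 0.25 / 1.5 = 0.33. The gain in precision is modest. The main point is that missing at random is more credible once on-treatment response is conditioned on.

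**5. Dropouts who fare worse than predicted (assumed).** With arm in the model, bias = (difference in dropout) × (shift of dropouts from prediction), in favour of the arm that loses more. The article gives neither quantity.

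| Dropout | Shift 0.3 SD | Shift 0.5 SD |
|---|---|---|
| 25% v 25% | 0 | 0 |
| 20% v 30% | 0.03 SD | 0.05 SD |
| 15% v 35% | 0.06 SD | 0.10 SD |

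In simulation, 15% v 35% with a 0.5 SD shift gave an estimate of −0.104 SD when the truth was 0, and a false-positive rate of 7%. When the arm losing more was truly 0.5 SD worse, power fell from 57% to 41%.

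**The case against.** The strongest reply is that the phrase is a loose translation of missing at random. The same paragraph abbreviates multiple imputation and estimating equations oddly and labels the arms differently from the rest of the article. Imputing from recorded data also points that way. This is a fair reading, and under it therapy-dependent dropout is no contradiction, provided arm is in the model. But arm is not among the inputs listed, so the reply answers the label and leaves the attenuation in place. A fuller plan may add arm. The sentence as published does not.

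A reader might go further and infer that the plan flatters whichever therapy loses more patients, or denies TBCT a retention advantage it is expected to have. The documents do not support that:
- The TBCT evidence is that "the dropout rate was lower in the TBCT group than in the PE group", and prolonged exposure is not an arm of this trial.
- The Introduction links the wide range of dropout rates to the population studied. No section predicts different dropout among TBCT, MBHP and PPT, or says how dropouts fare.
- The article does not say that patients who stop therapy are no longer assessed, so stopping and having a missing score are not the same thing.
- The 0.03 to 0.10 SD in step 5 is one assumed number times another. At 15% v 35% dropout the standard error is about √(0.75/38 + 0.75/29) = 0.21 SD, so 0.10 SD is about half a standard error. The planned chi-square test would also examine an imbalance in dropout.

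Nor is the lack of a sensitivity analysis an error in itself: the statistical analysis plan is not shown and may contain one.

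**Conclusion.** The point holds for the rule as stated. Its literal wording does not fit the article's premise about dropout. On either reading, the listed inputs ignore arm and mid-treatment response. Followed as written, between-arm CAPS-5 differences shrink by about the fraction missing: roughly 25% at the planned loss, or 0.5 SD to about 0.375 SD. This assumes that the input list is complete, that a quarter of final scores are missing in each arm, and that a two-arm end-of-treatment comparison stands in adequately for the planned model.

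Bias from informative dropout is a secondary possibility. It is small over the range shown, is zero if dropout is equal, and rests wholly on assumed values.

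**What to change.** In section 2.15, replace "assuming the random chance mechanism" with: missing at random given treatment arm and all observed scores, including session-7 CAPS-5. Add arm and those scores to the imputation model alongside the variables already listed.

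Add one pre-specified delta-adjusted analysis of end-of-treatment CAPS-5. Shift the imputed values by 0.1 to 0.5 SD in the worse direction, first equally in all arms and then in one arm at a time, and report the shift at which the conclusion changes. If the statistical analysis plan already contains such an analysis, a reference to it is enough.

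The cost is a sentence or two of text and a rerun of an imputation already planned. Recruitment, visits and treatment are untouched. The downside is slightly more analysis work and the chance that a borderline result is shown to be fragile.

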### 2.9. Instruments

Diagnostic assessment

Structural Clinical Interview for the DSM-5 (SCID-5) [63]: It is a semi-structured psychiatric interview, with the purpose of providing a diagnosis, according to the Diagnostic and Statistical Manual of Mental Disorders (DSM-5).

*PCL-5 PTSD Check List 5:* It contains 20 items with the purpose of assessing PTSD symptoms, in accordance with criteria B, C, D and E (DSM-5). Each item is scored on a scale that ranges from 0 (not at all) to 4 (extremely) [47,48,49]. This scale will be applied only at intake.

Primary outcome

Clinician-Administered PTSD Scale (CAPS-5) [64]: It is a diagnostic interview scale with 30 items to assess the diagnosis and severity of PTSD symptoms in accordance with DSM-5 [65,66]. CAPS-5 will be applied at baseline, mid-treatment (session seven) and post-treatment (session fourteen), as well as at follow-up (3, 6 and 12 months).

Secondary outcome

*Hospital Anxiety and Depression Scale* (HADS) [65]: This is a 14-item scale used to determine anxiety and depression symptoms, where each item is worth 0 to 3 points, and a total score of 9 or higher suggests mild symptoms. It was translated and validated for the Brazilian population [67,68]. This scale will be administered at baseline (initial evaluation), mid-treatment (week 7) and post-treatment (week 14), as well as at 3-, 6- and 12-month follow-ups.

*The World Health Organization Five Well-Being Index (WHO-5):* This is an overall well-being scale, with five questions and scores ranging from 0 to 5, addressing mood and energy [69,70]. The WHO-5 validation study into Brazilian Portuguese included 1128 individuals. During this research, the instrument presented good internal validity (Cronbach’s alpha = 0.83) [71]. WHO-5 will be applied at baseline, mid-treatment (session seven) and post-treatment (session 14), as well as at the follow-ups (3, 6 and 12 months).

Mediator variables

Trauma-Related Guilt Inventory (TRGI) [72]: This is a 32-item questionnaire assessing the cognitive and emotional aspects of guilt that are associated to a specific traumatic event. TRGI will be applied at baseline, mid-treatment (session 7) and post-treatment (session 14), as well as at the follow-ups (3, 6 and 12 months).

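### Section 2.15 enters time as a covariate in the GEE and names no visit contrast or baseline CAPS-5 adjustment; read literally, this is one linear trend that poorly captures the session-14 difference

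*Protocol article*

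**What the plan says.** Section 2.15 names the software, "Statistics Package for Social Science software (SPSS), version 24.0", and one model for the outcomes: "Generalized estimation equations (GHG), taking time as a covariate, will be performed to compare changes in scores over time and between groups". It adds: "The assumed level of statistical significance will be 0.05". It does not say how time is coded, which visits enter, whether there is a group-by-time term, or which contrast answers the primary question. Baseline data are mentioned only for the imputation, "with five imputed databases taking baseline and sociodemographic data".

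Section 2.8 defines the primary outcome without a time point: "Primary outcomes will be assessed by the reduction in PTSD symptoms, measured through CAPS-5". Section 2.9 gives the schedule: "CAPS-5 will be applied at baseline, mid-treatment (session seven) and post-treatment (session fourteen), as well as at follow-up (3, 6 and 12 months"). Section 2.1 puts treatment at 14 to 17 weeks, followed by visits out to 12 months. Section 2.10 sizes the trial on "three measures (baseline, mid-treatment and final assessment"), "for an effect size of 0.25", with a correlation of 0.50 between measures.

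**The concern.** SPSS GEE separates factors, which are categorical, from covariates, which are continuous. Taken at its word, Section 2.15 gives each arm a constant rate of change from baseline to the last visit entered. Therapy acts over about 14 weeks and then stops, so the gap between arms is unlikely to follow one straight line to 12 months. A comparison of slopes then depends heavily on what happens after treatment and may say little about the difference at session 14.

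The article is also silent on adjusting the CAPS-5 comparison for baseline CAPS-5, which every patient has before randomization. If baseline is only the first repeated outcome, the comparison amounts to a change score, which is less precise.

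At stake is whether the one stated test measures what the trial is sized to detect. A later analysis plan could add detail, but categorical visits would have to replace the present statement, because they do not follow from it.

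**Working it through.** **The plan's own figure.** For the between-groups repeated-measures F test, the noncentrality is f²·N·m/(1+(m-1)ρ). With f = 0.25, N = 108, m = 3, ρ = 0.50 this is 0.0625 × 108 × 3 / 2 = 10.125. The critical F(2, 105) is 3.08 and power is 0.81; N = 105 gives 0.797. So 108 reproduces.

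**Inputs for the check.**
- From the documents: ρ = 0.50; 135 patients, 25% dropout, three equal arms, so 135 × 0.75 / 3 = 33.75 per arm.
- Pairwise d: if two arms are equal and differ from the third by d SD (the pattern of H1), f = d√2/3, so f = 0.25 gives d = 0.25 × 3/√2 = 0.53.
- Assumed: visits at weeks 0, 7, 14, 27, 40, 66 (follow-ups from end of treatment); correlation 0.50 between all visits; two-sided 5% test; normal approximation; a true gap of 0.5 at week 7 and 1 at week 14, in units of the session-14 gap.

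**Literal model, all six visits.** Mean time is 25.67 weeks and Sxx = 2977.3. The fitted slope of the gap is b = Σ(t - 25.67)·gap / Sxx. With complete data, independence and exchangeable working correlations give the same b. SE of the slope difference = √(2(1-ρ)/(n·Sxx)) = √(1/(33.75 × 2977.3)) = 0.00315 SD per week. The test statistic is z = 0.53·b/SE.

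| Gap at weeks 0, 7, 14, 27, 40, 66 | Σ(t - 25.67)·gap | 14·b | Fitted gap at week 14 | z | Power |
|---|---|---|---|---|---|
| Sustained: 0, 0.5, 1, 1, 1, 1 | 35.00 | 0.16 | 0.61 | 1.97 | 0.51 |
| Halves: 0, 0.5, 1, 0.9, 0.75, 0.5 | 11.12 | 0.05 | 0.56 | 0.63 | 0.10 |
| Vanishes: 0, 0.5, 1, 0.75, 0.5, 0 | -12.83 | -0.06 | 0.51 | -0.72 | 0.11, mostly in the wrong direction |
| Grows: 0, 0.5, 1, 1.125, 1.25, 1.5 | 58.92 | 0.28 | 0.66 | 3.32 | 0.91 |

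The columns 14·b and fitted gap differ because the line places part of the gap at baseline, where none exists. In the sustained case the mean gap is 0.75, so the fitted baseline gap is 0.75 - 0.01176 × 25.67 = 0.45, and 0.45 + 0.16 = 0.61.

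**Coding matters too.** With visit number 0 to 5 as the covariate, the slope-implied change at session 14 is 0.37, 0.18 and -0.01 for the first three profiles, with power 0.67, 0.21 and 0.05. Section 2.15 does not choose between the codings.

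**Only the three treatment-period visits.** Times 0, 7, 14 give Sxx = 98 and b = 1/14, so 14·b = 1.00: no dilution. SE = √(1/(33.75 × 98)) = 0.0174, z = (0.53/14)/0.0174 = 2.18, power 0.59.

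**Baseline adjustment at session 14.**
- Change score: variance factor 2(1-ρ) = 1.00; z = 0.53/√(2 × 1.00/33.75) = 2.18; power 0.59.
- Baseline-adjusted: factor 1-ρ² = 0.75; z = 0.53/√(2 × 0.75/33.75) = 2.51; power 0.71.
- The reduction is 25%. Put the other way, the change-score variance is 2/(1+ρ) = 1.33 times the adjusted one (1.54 at ρ = 0.3, 1.18 at ρ = 0.7).

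**The case against.** The strongest reply is that the straight line to 12 months is a reading and is not what the article states. Section 2.15 is loosely worded elsewhere: its abbreviations for GEE, multiple imputation and the arms do not match the terms used in the rest of the article. The word covariate may mean no more than a model term. Section 2.10 uses only baseline, mid-treatment and final assessment; if those three enter, dilution disappears for an effect that builds linearly. This stands, and the dilution figures are therefore conditional. It does not remove the point, because nothing in Section 2.15 limits the visits or fixes the coding.

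It is also fair that a gap still growing after treatment would favour the slope (0.91 against 0.71), and that baseline as the first repeated measure is a valid way to compare changes. Both stand. The missing adjustment is partly inferred from silence in a condensed article, and its cost is precision.

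Three stronger readings are tempting and not supported:
- A reader might infer that the end-of-treatment difference itself can reverse. In the profiles above only the slope changes sign; the fitted week-14 difference stays positive.
- A reader might take three sized measures against six scheduled ones as an error. Sizing on the treatment period while also collecting follow-up is ordinary practice.
- A reader might add that shared therapists inflate the error rate by a definite amount. The article gives no number of therapists, caseload or intraclass correlation, so no such figure can be drawn from it.

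**Conclusion.** The point holds as a badly fixed analysis model that should be corrected before outcome data are analysed; it does not make the trial invalid. On the literal reading with all six visits in weeks, slope-test power runs from 0.10 or less in the right direction to 0.91, depending on what happens after treatment. That makes it a poor primary test of a difference expected by the end of therapy. These figures rest on the assumed gap profiles, visit weeks and uniform correlation, and do not apply if only the three treatment-period visits enter.

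The baseline figure is firmer, since it uses the protocol's own correlation of 0.50: adjusting gains about 12 percentage points of pairwise power (0.71 against 0.59) at d = 0.53 and about 34 per arm. Taking session 14 as the target is also a judgement. It is the last of the three sized measures, but no section names a primary time point.

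**What to change.** In Section 2.15, replace the time-as-covariate statement with this specification:
- visit as a categorical factor with a group-by-visit interaction;
- post-baseline CAPS-5 as the response and baseline CAPS-5 as covariate;
- the adjusted group contrast at the final assessment (session 14) as primary;
- the 3-, 6- and 12-month contrasts as secondary, from the same model.

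This takes about two sentences and no new data, since baseline CAPS-5 is already scheduled for every patient. The costs are a few more parameters and the loss of a slope test that would be stronger if the gap kept growing after treatment. If the authors always meant time as a categorical term, the first item only clarifies their wording.
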